**Methods/design:**

This study is a randomized, sham-controlled, patient- and assessor-blinded trial and aims to evaluate the effect of OA in women with PMOP. We will recruit 104 women aged 45–70 years with a diagnosis of PMOP. Participants will be randomly allocated in a 1:1 ratio to the OA group and the sham acupuncture (SA) group. Both groups will receive real herbal medicine treatment as a basic treatment twice a day for 3 months, the OA group receives real acupuncture treatment and the SA group receives placebo acupuncture treatment (non-penetrating, sham skin-needle therapy, sham cupping). All patients will receive acupuncture treatment twice per week for 3 months. The primary outcome is bone mineral density (BMD) and the secondary outcomes include estradiol (E2), follicle-stimulating hormone (FSH), bone gla protein (BGP), bone alkaline phosphatase (BALP), total antioxidant capacity (TAC), advanced oxidation protein products (AOPP), PPARγ, β-catenin, FoxO3a levels, visual analog pain scale score (VAS), Traditional Chinese medicine (TCM) syndrome scores and quality of daily life score (QOL). Outcome measures will be collected at baseline, middle of the treatment (1.5 months), the end of treatment (3 months). The present protocol followed the SPIRIT guidelines and fulfills the SPIRIT Checklist.

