**Conclusion:**

This study will be conducted to compare the efficacy of OA versus SA. This trial should help to evaluate whether OA can effectively prevent and treat PMOP by improving the estrogen levels of postmenopausal women. The mechanism is to improve the imbalance of osteogenic differentiation and lipogenesis of bone-marrow cells under oxidative stress.

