### Outcome measures

Outcomes will be collected at baseline, the middle of treatment, after treatment, and follow-up 6 months after the completion of the treatment. The overview of the outcome measurement at the different time points is shown in Table 3.

**Table 3 Tab3:** Overview of study visits

		Study period						
		Enrollment	Allocation	Post allocation			Close out	Follow-up
	Time point (month)	− 1	0	1	2	3		6
Preparation	Enrollment							
	Informed consent	√						
	Eligibility screen	√						
	Allocation		√					
Intervention	OA			√	√	√		
	SA			√	√	√		
Assessment	Liver function Kidney function	√						
	T; BP; P; R	√		√	√	√		
	BMD	√						√
	E2; FSH	√						
	BGP; BALP	√						
	TAC; AOPP	√						
	FoxO3a; β-catenin PPARγ	√						
	VAS	√		√	√	√		√
	TCM syndrome	√			√			
	QOL	√			√			
	Adverse events						√	
	Data analysis						√	
	Fracture rate							√

*T* body temperature, *BP* blood pressure, *P* pulse rate, *R* respiration rate, *OA*, *SA*, *QOL* quality of life, *TCM* traditional Chinese Medicine, *VAS* visual analog scale, *PPAR*, *E2*, *TAC*, *AOPP*, *BGP*, *BALP*, *BMD*, *FSH*

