### Blood testing

Sex hormones. Fasting blood samples will be draw every month before and after treatment by the nurse. Chemiluminescence immunoassay (CLIA) will be used to determine serum sex-hormone levels include estradiol (E2), FSH (Model: Berne, Switzerland, ELECSYS2011).Antioxidant index. Before and after intervention, a 5-ml venous blood sample will be obtained under non-fasting conditions. Samples will be frozen at − 70 °C. Advanced oxidation protein products (AOPP), and total antioxidant capacity (TAC) (with 2,2-diphenyl-1-picrylhydrazyl (DPPH) oxidation) will be measured using the following methods: Walwadkar [18], Kataaha et al. [19], Girbal et al. [20], Kitajima [21] and Janaszewska et al. [22].Bone metabolism index. Fasting venous blood will be collected before treatment, one course of treatment and at the end of treatment, respectively. The enzyme-linked immunosorbent assay (ELISA) (biocell enzyme standard instrument) will be used to determine bone gla protein (BGP) and bone alkaline phosphatase (BALP) before and after treatmentPathway signaling proteins. Western blot will be used to detect the expression of β-catenin, FoxO3a and PPARγ2 protein in bone tissue (Multiskan spectrum, Shanghai, China, ThermoScientific, USA).Follow-up is at 6 months after the completion of the treatment. Follow-up will be performed by telephone to ask if the participants have sustained any new fracture or have experienced recurrence of pain.

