### Data analysis

The analysis data set will consist of an intention-to-treat data set, a per-protocol (PP) data set, and a safety data set. The intention-to-treat data set will include all subjects assigned to each group. The PP data set will include only participants who adhered to the study protocol and completed the clinical study. The minimum compliance rate for participants taking the acupuncture treatments in the PP data set is 80%. The safety data set will include any participants who were randomly assigned to, and received, at least 1.5 months of the acupuncture treatments. The intention-to-treat analysis will be the primary analysis and will be compared with the PP analysis in a sensitivity analysis. The last-observation-carried-forward method will be used to manage missing data.

All collected data results were compiled using the SPSS 21.0 statistical software package, and collated, checked and statistically analyzed. The comparison between the data groups was performed by using a *χ*^2^ test, and the measurement data was consistent with the normal distribution and the homogeneity of the variance. The mean ± standard deviation ($$\overline{\mathrm{x}}\pm \mathrm{S}$$) indicates that the rank-sum test is used for comparison between grade data sets that do not satisfy the normal distribution and the homogeneity of the variance. *P* < 0.05 was significant for the difference. The variance analysis will be performed for the difference between the two groups and within the group. We will perform a regression analysis to examine the causal relationship between the E2, TAC and β-catenin, and the primary outcome. The statisticians who are independent of the research team will conduct the data analysis.

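### The marker regression is called causal but can show only association, and the pathway proteins are assigned to bone tissue although only blood collection is described

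*Protocol article*

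**What the plan says.** Mechanism is an aim of the trial beside efficacy and safety (Introduction, last paragraph; Discussion). The hypothesis is that acupuncture raises estrogen and corrects an oxidative-stress imbalance in bone-marrow cells. The abstract's Conclusion already words this as settled: "The mechanism is to improve the imbalance of osteogenic differentiation and lipogenesis of bone-marrow cells under oxidative stress".

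The one analysis written specifically for mechanism is in the Data analysis section: "We will perform a regression analysis to examine the causal relationship between the E2, TAC and β-catenin, and the primary outcome". The sentence does not mention treatment arm, covariates, time order or a mediation model.

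The Blood testing section describes three collections, all of blood:
- Sex hormones: "Fasting blood samples will be draw every month before and after treatment by the nurse".
- Antioxidant index: "a 5-ml venous blood sample will be obtained under non-fasting conditions", before and after the intervention.
- Bone metabolism: "Fasting venous blood will be collected before treatment, one course of treatment and at the end of treatment, respectively".

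For the pathway proteins, the same section says: "Western blot will be used to detect the expression of β-catenin, FoxO3a and PPARγ2 protein in bone tissue". The abstract lists these proteins as secondary outcomes and gives the timing for all outcomes: "Outcome measures will be collected at baseline, middle of the treatment (1.5 months), the end of treatment (3 months"). Table 3 has a row "FoxO3a; β-catenin PPARγ".

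**The concern.** There are two separate faults.

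First, randomisation protects the comparison of the two arms. It does not protect a comparison of women with high and low marker values. Age or severity of disease, for example, could move both a marker and BMD. A significant coefficient would then be reported as causal support for the mechanism although it could arise with no treatment effect.

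Second, three listed secondary outcomes, one of them a named regressor, are tied to a specimen whose collection is not described. Either the specimen is misnamed or a sampling procedure is absent from the schedule and the safety text. In both cases a reader cannot tell what the β-catenin term in the regression would be.

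**Working it through.** **Part 1: what the regression can show.** The plan gives no figure to reproduce, so this is an illustration with assumed inputs.

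From the documents: 104 participants enrolled, 42 per group (84 in all) required, significance at p<0.05.

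Assumed, not in the documents: the marker M has no effect on BMD (Y). One unmeasured patient factor U loads g on both. Acupuncture shifts M by 0.5 SD and does not change Y.

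Model, with T = 0 or 1 in equal halves and independent standard normal errors:
- M = 0.5T + gU + √(1−g²)·e₁
- Y = gU + √(1−g²)·e₂

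Closed form:
- Var(M) = 1 + 0.5² × 0.25 = 1.0625, and Cov(M,Y) = g².
- Induced correlation r = g²/√1.0625, which is 0.087, 0.243 and 0.475 for g = 0.3, 0.5 and 0.7.
- With n = 104, atanh(r) × √101 = 0.88, 2.49 and 5.20.
- P(p<0.05) = Φ(value − 1.96) + Φ(−value − 1.96) = 14%, 70% and 99.9%.

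Simulation by ordinary least squares, 2,000 trials per setting, share with p<0.05 for the marker although its true effect is zero:

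| Model | g = 0.3 | g = 0.5 | g = 0.7 |
|---|---|---|---|
| n = 104, marker only | 14% | 70% | 99.9% |
| n = 104, marker and arm | 15% | 73% | 99.9% |
| n = 84, marker only | 14% | 61% | 99.7% |

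An analysis supporting a causal reading would show about 5% in every cell. Adding the arm alone does not help, because the confounding lies between patients within arms. Nor does the result need acupuncture to move the marker: with no shift, r = g² = 0.09, 0.25 and 0.49, slightly higher than above.

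**Part 2: the specimen.** No arithmetic applies; the places are set side by side.

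| Place | What it says about the specimen |
|---|---|
| Blood testing, sex hormones, antioxidant and bone metabolism items | blood |
| Blood testing, pathway proteins | bone tissue; no collection described |
| Table 3 | a row for the proteins; no row for a bone sample |
| Interventions | no bone sampling |
| Adverse events | hematomas, burns, skin infections, acute pain; nothing tied to bone sampling |

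The heading and the described collections point to blood; the pathway-protein sentence says bone. Estradiol and antioxidant capacity are not affected. Of the three regressors, only β-catenin is.

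**Part 3: timing.** In the extracted Table 3 the hormones, antioxidant markers and pathway proteins are ticked at month −1 only. The abstract and the Blood testing section put the hormone and antioxidant measurements before and after treatment. Other rows show the same pattern. Liver and kidney function are ticked at screening only, although the Adverse events section repeats them after 12 weeks. BMD has no end-of-treatment tick, although the Primary outcome section measures it after treatment.

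**The case against.** The strongest reply has four parts.

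- **This is a condensed article.** Specimen procedures and model details may sit in the full protocol or a statistical analysis plan. This stands in part. A reader might infer that bone is never collected and that β-catenin cannot be measured. The article does not support that: it is silent on collection, and Table 3 schedules a measurement. What is on the page is a contradiction. Likewise the regression may be better specified elsewhere, but any later document would still have to withdraw or qualify the word *causal*.
- **Arm comparisons are already planned.** This stands. The markers are secondary outcomes, and the Data analysis section plans an analysis of variance between and within groups. The regression is therefore not the only evidence bearing on mechanism, and it would be wrong to say that the hypothesis rests on it alone.
- **The percentages are not trial evidence.** This stands as to size. The loadings are assumed, the simulation has one marker rather than three, and modelling BMD change or adjusting for baseline BMD would weaken the effect of a stable shared cause. The direction does not depend on these choices.
- **Table 3 shows baseline markers only, so the arm effect on them could not be estimated.** A reader might infer this stronger point. The text of the abstract and the Blood testing section contradicts it, and ticks may have been lost when the table was extracted.

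**Conclusion.** Both faults hold as stated here. The regression supports a statement of association, not causation. How misleading the causal label would be depends on unmeasured confounding: 14% to 99.9% false support at n = 104 for assumed loadings of 0.3 to 0.7, against a nominal 5%. That range shows direction and sensitivity; it is not an estimate for this trial.

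The specimen for β-catenin, FoxO3a and PPARγ2 contradicts its own section and has no counterpart in the schedule or safety text. This affects three secondary outcomes and one of three regressors.

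The primary BMD comparison between arms is untouched. The point should be corrected because mechanism is a stated aim and the abstract already words it as a conclusion. The documents do not support saying that the proteins are unmeasurable or that the arm effect on the markers cannot be estimated.

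**What to change.** 1. In the Data analysis section, delete *causal* and call the regression an exploratory association, with arm, baseline BMD and age in the model. These covariates reduce confounding but do not license a causal reading. Alternatively, report a mediation analysis with its no-confounding assumption stated. Limit the mechanism statements in the abstract and Discussion to match.
2. Rest the mechanism evidence on the randomised comparison of end-of-treatment estradiol, FSH, antioxidant capacity and oxidation protein products, each adjusted for its baseline value. This refines the between-group analysis already planned and uses data already collected.
3. Reconcile the specimen for the pathway proteins with the section heading, the visit schedule and the safety monitoring. If no such specimen is obtained, remove the three proteins from the outcomes and β-catenin from the regression.
4. Check the Table 3 ticks for these markers against the abstract and the Blood testing section.

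The cost is wording and a few extra models. The mechanism claim becomes more modest.

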### Data monitoring

The Data Monitoring Committee (DMC) of Dali University which is independent from the sponsor and any competing interests will conduct regular monitoring to ensure the quality of the data. Its monitors check that the randomly assigned study participants meet the inclusion and exclusion criteria and that the study is proceeding well, and they ensure that the data is adequately recorded in the case report forms. There will be no interim analysis. The study will continue until the 104 participants have completed the study.

### Adverse events

Safety will be assessed by body temperature, pulse rate and character, respiratory rate, blood pressure, renal function test, and liver function test. These indicators are detected during the period of screening and after 12-week treatment. We will monitor adverse events for each treatment during the trial, including hematomas, skin burns, skin infections and acute pain. Any adverse events or reactions that are thought to be causally associated with the intervention will be recorded, managed, and reported to the study coordinators. Serious adverse reactions will be reported to the Ethical Committee.

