### Sample size and blinding

According to the preliminary research [15], we hypothesize that the effective rate after OA is 77.8% and the effective rate after SA is 50%. The equation that we used for this was *α* = 0.05, *β* = 0.20 and we determined that a sample size of 42 patients in each group would be sufficient to detect the statistical difference between the two groups, allowing for a 20% withdrawal rate. We will plan to enroll a total of 104 participants with 52 participants in each group. According to the random number sequence generated by computer, the patients will be randomly divided into either the OA group or the SA group in a 1:1 ratio.

The participants, outcome assessors, study monitors, data managers, and statisticians will be blinded to treatment allocation. If possible, the study participants will be advised to avoid discussing the investigational treatments with other participants. Blinding will be maintained until the 104 participants have completed the study. The success of double-blinding will be assessed at the final visit. Due to the special nature of acupuncture, acupuncturists cannot be blinded to the treatment. The database will then be locked. An emergency code for each individual has been provided to the study researchers and will be disclosed only if it must be known whether a patient is receiving acupuncture treatment or SA in order to manage a serious adverse event.

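### Adverse events are recorded only if someone suspects the intervention caused them, so unexpected harms can be lost in both arms and the filter could differ between arms

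*Protocol article*

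**What the plan says.** Three sentences in the Adverse events section set the rules.

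- Surveillance: "We will monitor adverse events for each treatment during the trial, including hematomas, skin burns, skin infections and acute pain".
- Recording: "Any adverse events or reactions that are thought to be causally associated with the intervention will be recorded". The same condition governs management and reporting.
- Serious events: "Serious adverse reactions will be reported to the Ethical Committee".

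The same section lists safety measures that need no causality opinion: vital signs, renal function and liver function.

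The section on sample size and blinding says "Due to the special nature of acupuncture, acupuncturists cannot be blinded to the treatment". It also says "The participants, outcome assessors, study monitors, data managers, and statisticians will be blinded to treatment allocation". Neither section says who decides whether an event is causally associated.

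Table 3 ("Overview of study visits") has one tick in its adverse-event row, in the close-out column. Fracture rate is ticked at follow-up, and the follow-up telephone call described under Blood testing asks about new fractures and recurrent pain.

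The Introduction names safety, with efficacy and mechanism, as something the trial will study. The Discussion repeats this.

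**The concern.** A randomised comparison of harms is sound when events are counted in the same way in both arms and attribution is considered afterwards. Here attribution comes first and decides what enters the record.

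Two things follow. First, an event nobody links to the intervention need not be written down, and unexpected harms are by definition the ones nobody is looking for. That loss can occur in both arms, and it cannot be repaired at analysis. Second, if the person giving the opinion knows the arm, or is told by someone who does, the share of events passing the filter may differ between arms. The recorded difference would then mix real harm with belief about harm.

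The primary outcome, BMD, is not touched. What is at stake is the safety conclusion.

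**Working it through.** **Reading the rules together.** The surveillance sentence covers adverse events in general, but it promises monitoring, not recording. The next sentence is the only one that says what is recorded, and it carries a restrictive clause on causality. The serious-event sentence is limited to reactions. No other section states that all events are recorded regardless of cause. So the plain reading is that an unsuspected event may be seen and left unrecorded.

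**Who applies the filter.** The article names no one. The listed events (hematomas, burns, infections, acute pain) arise from procedures that the unblinded acupuncturists perform, so they are well placed to see them. A blinded assessor could still give the opinion.

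**Size.** The article gives no adverse event rate and no attribution share, so there is no planned figure to reproduce. What follows is illustration with assumed inputs. Only the 52 per arm comes from the protocol (Sample size and blinding).

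Formula: recorded proportion = (women with an event × share judged causal) / 52. Assume that 10 women in each arm have one event, so the true difference is 0.

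| Share judged causal, OA v SA | Recorded, OA v SA | Difference, OA − SA |
|---|---|---|
| 50% v 50% | 5/52 v 5/52 | 0 |
| 60% v 40% | 6/52 = 11.5% v 4/52 = 7.7% | 3.8 points |
| 80% v 40% | 8/52 = 15.4% v 4/52 = 7.7% | 7.7 points |
| 80% v 20% | 8/52 = 15.4% v 2/52 = 3.8% | 11.5 points |
| 20% v 80% | 2/52 v 8/52 | −11.5 points |

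The size also depends on the assumed event rate. At 80% v 40% the spurious difference is the true rate × (0.80 − 0.40). A true rate of 10% in both arms gives 4 points, and 50% gives 20 points.

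**A filter can hide harm as well as create it.** Assume true rates of 30% (OA) and 10% (SA), that is 15.6 and 5.2 expected women.

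- With full recording the difference is 20 points, and power at 52 per arm (two-sided 0.05) is about 73%.
- If one third of OA events and all SA events are judged causal, 15.6 × 1/3 = 5.2 against 5.2, and the true difference vanishes.
- If half are judged causal in both arms, 15% v 5% remain. The difference is halved to 10 points and power falls to about 40%.

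The last case has no arm-dependent bias at all. The filter still does damage.

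**The case against.** The strongest reply is that the recording sentence is being made to carry too much. A reader might infer that unblinded acupuncturists judge causality and will blame real needling more readily than the blunt needle. The article supports neither step: it names no judge, it blinds participants, outcome assessors and study monitors, and nothing in it fixes the direction of any bias. This part of the reply stands, so a differential filter is a possibility and not a stated feature of the design.

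Other stronger readings also fail.

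- A reader might infer that herb-related events escape recording. The herbal medicine is described under Interventions, so such an event may count as associated with the intervention, and liver and renal tests could reveal some herbal harm regardless of opinion.
- A reader might infer that all safety data are filtered. Vital signs, laboratory tests and follow-up fractures are not.
- A reader might take Table 3 to mean that women are asked about adverse events once. The close-out column ticks adverse events alongside data analysis, so it may simply mean compilation at the end of the study.
- A reader might take 11.5 points as an estimate of bias in this trial. It is the result of one assumed split.

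It can also be said that an article leaves the details of safety reporting to the full protocol, and that one word, reactions, is thin evidence in a condensed text. That weakens the point on serious events somewhat. It does not remove the main one: the article does not omit the recording rule, it states one, and that rule is conditional on suspected cause. Even a fully blinded judge would leave the condition in place.

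**Conclusion.** The point holds in a limited form. As written, recording and reporting of adverse events depend on suspected causality, and only serious reactions are named for the Ethical Committee. Unexpected or misattributed events can therefore be lost in both arms. Because the person who assesses causality is unnamed and the treating acupuncturists are unblinded, the loss could also differ by arm, with the direction unknown.

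The actual size cannot be determined from the article. Under the assumption of 10 women with an event per 52 in each arm, the spurious difference runs from 0 through about 8 to about 12 points as attribution moves from equal to 80% v 20%, and it changes sign if attribution is reversed. The conclusion rests on reading the causality clause as restrictive, which is its plain sense, although the article does not itself use the word only. This is a cheap improvement to a declared aim of the trial and does not threaten the primary analysis.

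**What to change.** Amend the Adverse events section as follows.

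1. Record every adverse event and serious adverse event in both arms at each visit, whatever the suspected cause, with onset, severity and seriousness.
2. Record causality as a separate field, completed by one of the assessors who is already blinded.
3. Report all serious adverse events, not only those judged to be reactions.
4. Tabulate all-cause events by arm first, and events judged related second.
5. Align the adverse-event row of Table 3 with the per-treatment monitoring that the text promises.

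The cost is a slightly longer case report form at visits already held. No extra staff or visits are needed.
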